### Potential challenges

Patients will be recruited during the first days of hospital admission. Many patients may not be able to give consent or, even if they are, be unwilling to participate in the study because they are severely distressed. A number of patients admitted during the weekend and discharged after a few days may be difficult to contact. In order to enable researchers to promptly screen all admitted patients, we have established close links with the hospital staff. Presentations/refreshers on the study at all sites are carried out to make sure that all the clinical staff in the hospitals are informed on the study and information on new admissions is quickly passed on to the researchers.

One important challenge for the follow-up relates to the different ways in which medical records are stored in different countries. In UK and Italy, continuous electronic medical records, including information on a given patient within and outside the hospital, are available; however, this is not the case in other countries. Therefore, patients will receive short phone interviews at follow-up in Germany, Belgium and Poland. This may determine attrition rates higher than 15% for the primary outcome in these countries; in UK and in Italy, attrition rates are likely to be lower than 15%. The potential imbalance in missing data at follow-up among countries will be controlled in the mixed model adjusting for fixed effect of baseline patient-level variables and random effects at a hospital level.

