#### Other clinical and social outcomes

*Clinical outcomes* including: (1) number of readmissions; (2) number of compulsory readmissions; (3) inpatient bed days, using an ad hoc schedule based on the Client Service Receipt Inventory.^30^*Social outcomes,* based on the SIX index,^31^ which captures*:* (1) employment (none; voluntary or protected or sheltered work; regular employment); (2) accommodation (homeless or 24 h supervised; sheltered or supported accommodation; independent accommodation); (3) living situation (living alone; living with a partner or family); (4) contacts with friends (not having met a friend within the past week; having met at least one friend in the past week).*Subjective quality of life*, measured by the Manchester Short Assessment of quality of life MANSA.^32^*Untoward incidents related to mental healthcare*, including: (a) deaths; (b) completed suicides; (c) serious assaults committed by patients; (d) physical violence experienced by patients; (e) suicide attempts; (f) serious side effects from pharmacological treatment requiring hospitalisation, as extracted from clinical records or obtained through phone interviews.*Social contacts,* measured as: (a) the total number of social contacts within the week preceding the assessment as reported by patients using an ad hoc instrument, adapted from the Social Network Schedule,^33^ and (b) whether or not they declare to have at least one close friend, using the specific item on the MANSA.^32^*Experienced discrimination,* measured as*:* (a) patient-reported episodes of discrimination because of mental illness, and (b) patient-reported avoidance of activities because of fear of discrimination, measured by ad hoc items.*Perceived socioeconomic status,* that is, patient self-rated standing in his/her own self-defined community and country, measured by the MacArthur Scale of Subjective Social Status.^34^
^35^

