#### Data collection at one-year follow-up

Clinical outcomes, employment, accommodation, living status, friendships, untoward events and indicators of care costs will be followed up for the *entire sample* via *medical records or telephone contact*.

To assess patients’ subjective quality of life, global social contacts, experienced and anticipated discrimination, perceived socioeconomic status, satisfaction with care, contacts with primary and secondary care professionals, and for patients’ experienced continuity of care we will randomly select a *subsample of patients, who will be interviewed face-to-face*.

Patients and clinicians interviewed for the *qualitative study* will be purposively selected from among those included in the entire sample. Selection criteria are reported in the following paragraph.

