### Sample size determination

The sample size for the quantitative study was calculated with the aim to detect a 5% difference in rates of re-admissions (ie proportion of patients re-hospitalised during the one year follow up) between the two care approaches from 27.5% to 32.5% with 80% power at the 5% significance level.

The sample size required for an individual-level comparison not considering clustering of outcomes within centres and hospital would be 2716 patients.

We calculated an average cluster size per hospital of 150 patients recruited over one year. Taking into account a 15% drop out rate, the average number per hospital of patients recruited and followed up will be 128. The variance inflation factor (or design effect, IF) is given by IF=1+(m−1)×ρ; where m=cluster size, and ρ=ICC (inter-cluster correlation coefficient). The ICC in a cluster with such a large number of patients is expected to be very small.^37^ With m=128 and ρ=0.007, IF is 1.90, and the adjusted sample size is N=5162 (1034 per country), requiring eight hospitals per country with an average number of 150 patients recruited per hospital, ie 1200 patients per country and 6000 overall.

We will carry out follow-up face-to-face interviews with a subsample of patients who will be 18–65 years of age. The patients will be stratified based on diagnostic group (ICD codes: F20–29, F30–39, F40–49)^27^ and on whether the index admission was their first one or they have had previous hospital admissions. We will aim to interview 30 patients per stratum, resulting in 360 patients per country (60×6 clusters) and an overall sample of 1800 patients (360×5 countries).

For the in-depth interviews, we will purposively select 40 patients and 13 clinicians in each country, resulting in a total sample of 200 patients and 65 clinicians.

Within the sample, there will be a mix of: (1) patients treated with ‘specialisation’ and ‘personal continuity’ of care approaches; (2) those who were rehospitalised during the follow-up and those who were not; and (3) patients with different diagnoses (F20–29, F30–39, F40–49).

Clinicians will be included taking into account: (1) the care approach (‘specialisation’ or ‘personal continuity’) adopted by the service they work within and (2) their qualification: psychiatrists, psychologists, nurses/social workers.

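### The mixed model cannot control missing readmission data that depend on readmission itself, as may happen in the three countries followed up largely by phone

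*Protocol article*

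**What the plan says.** Under Potential challenges, the article explains that the UK and Italy have continuous electronic records spanning care inside and outside hospital and the other three countries do not. As a result, "patients will receive short phone interviews at follow-up in Germany, Belgium and Poland". It expects attrition on the primary outcome possibly above 15% in those three countries and probably below 15% in the UK and Italy. It then gives the remedy: "The potential imbalance in missing data at follow-up among countries will be controlled in the mixed model", by baseline patient-level fixed effects and hospital-level random effects.

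The covariates listed under Analysis of clinical and social outcomes are age, gender, diagnostic group, previous admission, severity, social situation and formal status, all fixed at or about the index admission. Random effects are for hospitals, or for approach clusters within hospitals in Germany, Belgium and Poland.

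On data sources, Data collection at one-year follow-up says that clinical outcomes, "untoward events and indicators of care costs will be followed up for the" whole sample through either medical records or telephone. Untoward incidents, which include deaths and completed suicides, are taken "as extracted from clinical records or obtained through phone interviews".

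**The concern.** The primary outcome is a single yes/no per patient over one year. No earlier outcome measurement can inform the model about a patient who is lost, so that patient adds nothing to the likelihood. Adjustment then deals only with missingness that the baseline covariates, approach and hospital explain.

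In the phone countries, a patient who is back in hospital, unwell or without stable housing is plausibly harder to reach. A patient who has kept the same clinician may be easier to trace. In these three countries approach is set patient by patient, through insurance, team decision or patient choice, so reachability could differ by approach within one hospital. This is reasoning about mechanism; the article gives no figure for it.

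At stake is the primary comparison in three of five countries, 3 × 1200 = 3600 of the 6000 planned patients. The safety comparison is also affected: a patient who has died cannot be interviewed, and continuous records are lacking in the same three countries.

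**Working it through.** **The plan's own figure.** The design target is a difference "between the two care approaches from 27.5% to 32.5% with 80% power at the 5% significance level". For 27.5% vs 32.5%, two-sided 5%, 80% power, the normal-approximation formula gives 1318 per group, and 1358 with continuity correction. 2 × 1358 = 2716, the stated total. The design effect is 1 + 127 × 0.007 = 1.889 (stated 1.90), and 2716 × 1.90 = 5160 against the stated 5162. The sample size reproduces.

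**Loss of numbers is minor.** At 15% attrition everywhere, N = 5100 and power is 0.81. With 10% assumed in the UK and Italy and 30% in the phone countries, N = 2400 × 0.90 + 3600 × 0.70 = 4680 and power is 0.79. At 40% in the phone countries it is 0.77. The problem is bias.

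**When the odds ratio is biased.** Let r1 and r0 be the probabilities that a readmitted and a non-readmitted patient is followed up. Among patients followed up:

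observed rate = p·r1 / [p·r1 + (1 − p)·r0]

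observed OR (A vs B) = true OR × (r1A/r0A) / (r1B/r0B)

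The OR is unchanged if r1/r0 is equal in the two approaches, and biased if it is not.

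**Main illustration (assumed inputs).** True readmission is 30% in both approaches; attrition is 30% (A) vs 20% (B); 45% of those missed were readmitted. Observed rate = (true − attrition × rate among missed) / (1 − attrition).

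- A: (0.30 − 0.30 × 0.45)/0.70 = 0.165/0.70 = 23.6%
- B: (0.30 − 0.20 × 0.45)/0.80 = 0.210/0.80 = 26.2%
- False difference in the phone countries: 2.7 points, OR 0.87

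To pool, take three phone countries and two record countries of equal size, with 10% outcome-independent loss in the latter:

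- A: (3 × 0.165 + 2 × 0.27)/(3 × 0.70 + 2 × 0.90) = 1.035/3.9 = 26.5%
- B: (3 × 0.210 + 2 × 0.27)/(3 × 0.80 + 2 × 0.90) = 1.170/4.2 = 27.9%
- False pooled difference: 1.3 points

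With 60% readmitted among those missed, the phone-country rates are 17.1% vs 22.5% (5.4 points). Pooled, 0.90/3.9 = 23.1% vs 1.08/4.2 = 25.7% (2.6 points).

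**Sensitivity to the mechanism (assumed inputs).** True readmission is 30% in both approaches, and 80% of non-readmitted patients are reached in both.

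| Readmitted patients reached, A vs B | Observed, phone countries | Difference | OR | Pooled difference | Pooled OR |
|---|---|---|---|---|---|
| 60% vs 60% | 24.3% vs 24.3% | 0.0 | 1.00 | 0.0 | 1.00 |
| 60% vs 70% | 24.3% vs 27.3% | −3.0 | 0.86 | −1.6 | 0.92 |
| 60% vs 80% | 24.3% vs 30.0% | −5.7 | 0.75 | −3.1 | 0.86 |

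**Does adjustment help?** A simulation of the same three rows used 40 hospitals, a baseline covariate that predicts readmission, and hospital indicators standing in for random effects. The adjusted pooled ORs were 1.01, 0.91 and 0.85, against a true value of 1. Adjustment left the bias in place. Random effects for approach clusters within hospitals would not help either: they average to zero, so a systematic shift between approaches goes into the approach coefficient.

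**If a true effect exists.** Take 32.5% in A, 27.5% in B (OR 1.27), and the 60% vs 70% row. The phone countries then show 1.6 points (OR 1.09) and the pooled data 3.2 points (OR 1.17).

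**The case against.** Several stronger readings are tempting, and the documents do not support them.

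- *Unequal attrition among countries biases the comparison.* Not by itself, because both approaches exist in every country. Read narrowly, the article's sentence is only about imbalance among countries.
- *Outcome-dependent loss alone biases the result.* If the dependence is the same in both approaches, the odds ratio is untouched (first table row). Observed rates fall, and with 60% vs 80% reach a true 5.0-point difference shows as 4.4 in the phone countries. Bias in the OR needs dependence on outcome and approach together, and the article gives no evidence of that.
- *Deaths cannot be observed in three countries.* A reader might infer this from the phone interviews. But records are a permitted source for untoward incidents and for whole-sample follow-up, and the article says only that continuous records across settings are lacking. Under-ascertainment, differing by country, is as far as the text goes.
- *The missing sensitivity analysis is the fault.* An analysis plan not shown may contain one. The fault is the positive claim of control.

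It is also fair to say that every attrition and reach figure used here is assumed, and that admission of both approaches to the same hospital makes differential tracing less obvious. What stands is that the claimed property does not follow from the model described.

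**Conclusion.** The point holds in limited form. A mixed model with baseline covariates and hospital effects, applied to one binary outcome per patient, addresses missingness only under missing-at-random given covariates, approach and hospital. The article claims more, in the setting where that assumption is most open to doubt.

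Under the assumed scenarios with no true difference, the false difference is about 2.7 to 5.7 points in the phone countries and 1.3 to 3.1 points pooled, against the 5-point design target. It is zero if the dependence on readmission is the same in both approaches. The direction is unknown.

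For deaths and suicides, the supported conclusion is possible under-counting in Germany, Belgium and Poland and ascertainment that differs from the UK and Italy.

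**What to change.** 1. Replace the claim of control with a statement that the mixed model assumes missingness is at random given baseline covariates, approach and hospital. Add a delta-adjusted (tipping-point) sensitivity analysis that varies the readmission odds of non-responders separately by approach within the phone countries. Multiple imputation from the same baseline variables is no substitute, since it rests on the same assumption.
2. In Germany, Belgium and Poland, use the recruiting hospitals' own records, already a permitted source, for readmission and vital status in all patients there, reached or not. Limiting the look-up to unreached patients would measure the outcome differently in responders and non-responders. Report the outcome source by approach. Readmissions to other hospitals will still be missed, so item 1 remains necessary.
3. Report deaths and suicides by country and ascertainment source, with the UK and Italy alone as a sensitivity analysis.

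The cost is a modest record look-up at hospitals already taking part, some extra analysis, and a less reassuring statement about missing data. The article's status date is June 2015 and follow-up is planned to end by 31 December 2016, so most one-year follow-ups still lay ahead at that date.

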### Expected outputs

The dissemination of COFI results will not only follow the usual pathway of publications in scientific journals but also take advantage of electronic means of communication (newsletters, twitter, website and online journals).

Moreover, to facilitate the translation of findings into national mental healthcare policies and practices, we will: (1) produce recommendations for policy decision-making based on study findings; (2) organise workshops inviting all relevant stakeholders.

Recommendations on policy decision-making will be circulated to different stakeholders: (1) national governments; (2) professional associations; (3) carers and users groups; (4) opinion leaders, managers and policymakers at a national level. The stakeholders will be able to familiarise with study findings in order to make their contribution in translating research evidence from COFI into the practice of policy decision-making.

The organisation of national workshops in all the participating countries and of one European workshop to discuss COFI findings will allow direct contact with stakeholders. Such events will offer opportunities for feedback, as well as for the creation of strong relationships with stakeholders and interest groups that will enhance the impact of study findings on national mental health policies.

## Current study status

In June 2015, COFI is in the ninth recruitment month (out of 15 months). During the study period, 13 916 patients were admitted in the included hospitals. Among them, 8153 were eligible for the study (58.6%); 4484 of the eligible patients gave informed consent to participate in the study (55%). Eligibility and opt-in rates are similar to previous studies on hospitalised patients^38^
^50^ and the current recruitment rate is in line with the planned recruitment target (6000).
